### 2.2. Design and Settings

This trial is a randomized, double-blind, placebo-controlled clinical study, with 66 subjects planned to be enrolled. Informed consent will be signed after patients are screened by inclusion and exclusion criteria. The researchers will randomly divide the subjects into the QSYQ group and the blank placebo control group according to the time of enrollment. Before enrollment, there will be a 1-week screening period, during which other TCM drugs for CHD will be stopped. After entering the group, the patients will receive 12 weeks of medication. The flowchart of the research process is shown in Figure 1. All subjects will be followed up every 2 weeks after enrollment and will be monitored and evaluated at each follow-up. The technology roadmap is shown in Figure 2.

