#### 2.5.4. Sample Size Calculation

After interventional treatment for patients with coronary heart disease (CHD), according to the reference literature, the difference in the amplitude of the increase in peak oxygen consumption was 3.33 mL/(min(/), the standard deviation was 3.65 mL/(min(/), the error of class I was 0.05, and the test efficiency was 90%. The following formula was used to calculate the sample size of each group:(1)$$\begin{array}{c} n=\frac{2{\left(\mu_{\alpha }+\mu_{\beta }\right)}^{2}\sigma^{2}}{\delta^{2}}. \end{array}$$

The sample size of each group was 26; considering a 20% rate of shedding, 33 samples were calculated. According to the order of entering the group, 33 cases will be randomly divided into the QSYQ group and the blank placebo control group.

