### 2.7. Follow-Up

Following enrollment, all subjects will be followed up every 2 weeks, and the researchers set the content of each follow-up. After 8 weeks, all subjects will be followed up every 4 weeks until the end of the 12-week study. Follow-up will involve recording changes in TCM symptoms, Seattle scale score, and quality of life scale score.

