## 3. Outcome

The primary outcome is the rate of change of VO_2_ peak. The secondary outcomes are as follows: (1) assessment of target organ damage, including changes in systolic and diastolic function indices (left ventricular ejection fraction, stroke output, left ventricular end-diastolic volume, *E*/*E*′, left atrial volume, etc.) in echocardiography observed before and after treatment; (2) symptom improvement evaluation using the TCM syndrome observation table (Table 2); Seattle scale and quality of life scale will be used to evaluate angina pectoris symptoms and quality of life; and (3) routine laboratory examination indicators, including routine bloods, liver and kidney function, and blood lipids.

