### 3.3. Data Analyses

The international SAS version 9.4 statistical analysis software will be used for statistical analysis. The measurement data of each visit for different treatment groups will be statistically described by means of mean *u* standard deviation or median (minimum and maximum). Paired *t*-test will be used to compare the differences between the two groups. Changes before and after treatment in the two groups will be compared by analysis of variance or nonparametric test. The frequency (constituent ratio) will be used to describe the count data of each visit in different treatment groups. The changes before and after treatment in the two groups will be analyzed using the *χ*2 test, exact probability method, or nonparametric test. Except for special instructions, the bilateral test will be used to examine statistical significance, and *P* ≤ 0.05 will be used as the criterion for judging the significance of the difference.

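### The repeated Seattle and quality-of-life scores are tested only as an unadjusted before-after change; a baseline-adjusted repeated-measures model would use the same data better

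*Protocol article*

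**What the plan says.** Section 2.7 (Follow-Up) provides for repeated measurement: "Follow-up will involve recording changes in TCM symptoms, Seattle scale score, and quality of life scale score". Its schedule is two-weekly at first, and then "After 8 weeks, all subjects will be followed up every 4 weeks until the end of the 12-week study". Section 2.2 gives a different schedule: "All subjects will be followed up every 2 weeks after enrollment and will be monitored and evaluated at each follow-up".

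Section 3 lists these measures as secondary outcomes: "Seattle scale and quality of life scale will be used to evaluate angina pectoris symptoms and quality of life". TCM symptoms are assessed with Table 2, which sorts patients into response categories by percentage change in the syndrome score.

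Section 3.3 gives the per-visit data a descriptive role: "The measurement data of each visit for different treatment groups will be statistically described by means of mean" and standard deviation, or by median and range. The test of change is then "Changes before and after treatment in the two groups will be compared by analysis of variance or nonparametric test". Count data get chi-square, exact or nonparametric tests. No longitudinal model and no covariate is named. Section 2.5.1 sets two randomisation factors, sex and number of diseased vessels.

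The only stated attrition figure is in section 2.5.4, for peak VO2: "considering a 20% rate of shedding, 33 samples were calculated".

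**The concern.** The article names a test for these scores, so the point disputes a stated choice and does not complain of a missing detail. Three features of that choice cost information.

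- Subtracting the baseline is not the same as adjusting for it. Unless baseline and final score are almost perfectly correlated, the raw change carries avoidable noise.
- The intermediate scores play no part in the named comparison.
- A before-after change cannot be formed without a final value. If patients who do poorly leave early, a comparison of those who remain generally rests on a stronger assumption than a likelihood-based repeated-measures model, which is valid under missing at random.

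Quality of life is part of the trial's stated aim, and with 66 patients there is little precision to spare.

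**Working it through.** **Visits.** Section 2.7 gives weeks 2, 4, 6, 8 and 12, which is 5 post-baseline visits. Section 2.2 gives weeks 2, 4, 6, 8, 10 and 12, which is 6. Both are carried through below.

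**The plan's own figure.** With difference 3.33, SD 3.65, two-sided 0.05 and 90% power, n = 2(1.960 + 1.282)² × 3.65² / 3.33² = 25.25, rounded up to 26 per group. Then 26 / 0.8 = 32.5, rounded up to 33. The stated figures reproduce, but they concern peak VO2. No stated figure depends on the scales.

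**Assumptions, not in the documents.**
- 33 per arm, with 20% lost at random, spread evenly after each visit except the last. That leaves 33 × 0.8 = 26.4 per arm with a week-12 score.
- Unit variance at each visit.
- Correlation either exchangeable (0.60 or 0.75) or autoregressive (0.85 or 0.90 per 2 weeks).

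**Formulas**, with r the correlation between baseline and week 12 (for the autoregressive pattern, 0.85⁶ = 0.377 and 0.90⁶ = 0.531):
- Variance of the treatment difference from ANOVA on change: 2 × 2(1 − r) / 26.4.
- From a baseline-adjusted analysis (ANCOVA) of patients with a week-12 score: 2(1 − r²) / 26.4.
- The ratio of the second to the first is (1 + r) / 2. This is the effect of baseline adjustment alone.
- For the repeated-measures model, generalised least squares on the post-baseline scores given baseline, adding the information from patients who leave after each visit.

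| Assumed correlation | r | ANCOVA / change ANOVA | Repeated measures / change ANOVA, 5 and 6 visits | Effective n per arm given baseline, 5 and 6 visits |
|---|---|---|---|---|
| Exchangeable 0.60 | 0.600 | 0.800 | 0.765, 0.763 | 27.61, 27.69 |
| Exchangeable 0.75 | 0.750 | 0.875 | 0.828, 0.825 | 27.91, 28.00 |
| Autoregressive 0.85 | 0.377 | 0.689 | 0.654, 0.640 | 27.79, 28.38 |
| Autoregressive 0.90 | 0.531 | 0.766 | 0.718, 0.703 | 28.15, 28.75 |

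**Total gain.** The variance ratio runs from 0.64 to 0.83. Inverted, 1/0.83 = 1.20 and 1/0.64 = 1.56, so roughly 20% to 55% more information than the stated ANOVA.

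**Share due to interim visits.** 27.61 / 26.4 = 1.046 and 28.75 / 26.4 = 1.089, so about 5% to 9%. In every row the fall from 1 to the ANCOVA column is larger than the further fall to the repeated-measures column.

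**Sensitivity.** With r from 0.3 to 0.7 and some losses before the first visit, the repeated-measures model has 61% to 81% of the variance of ANOVA on change, and 92% to 98% of that of the ANCOVA. For an assumed standardised effect of 0.5, power is 0.34 to 0.65 (change ANOVA), 0.48 to 0.72 (ANCOVA) and 0.48 to 0.75 (repeated measures).

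These calculations treat the covariance as known and leave out sex and number of diseased vessels, whose effect on precision cannot be judged from the article.

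**The case against.** The strongest reply is that these are secondary outcomes, a single end-of-treatment contrast is a legitimate target, and choosing between two valid analyses is a matter of preference. That stands as a limit on severity. It does not remove the point, because the recommended model keeps the same week-12 target and estimates it more precisely from data already planned.

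Several stronger readings are tempting but not supported:

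- *Interim data are thrown away.* They are summarised by group at each visit. They are only absent from the named test.
- *Early leavers are excluded.* Section 3.3 states no analysis set or missing-data rule for these scores, and an analysis plan that is not shown may supply one. What follows from the text is only that a change score needs a final value.
- *The plan expects 20% of week-12 scores to be missing.* The 20% belongs to peak VO2. The shedding criteria in section 2.4.4 include no final exercise value, compliance below 80% and serious deviation, and such patients may still complete the questionnaires. The 20% used above is an assumption.
- *Everything is tested by ANOVA.* The sentence is generic and allows a nonparametric test. The TCM outcome also has a categorical form in Table 2, which would fall under the count-data tests.
- *The interim visits are the main loss.* A calculation that ignores baseline gives 28.4 to 30.4 effective patients per arm against 26.4, or 8% to 15%. That describes neither the stated test, which uses change from baseline, nor a model with baseline as covariate. With baseline included, the figure is the 5% to 9% shown above.

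A separate sentence in section 3.3 is wrong on its face: "Paired *t*-test will be used to compare the differences between the two groups". The groups are independent. It is a different matter, but it means this section needs revision anyway.

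**Conclusion.** The point holds as one of efficiency and robustness, at low severity. The article fixes an unadjusted before-after comparison for scores that are measured repeatedly, and a better analysis of the same data is available. The size of the gain rests wholly on assumed correlations and an assumed dropout pattern at random, since the article gives neither for these scales. The direction is firmer: (1 + r)/2 is below 1 for any correlation short of perfect, so baseline adjustment helps whatever the dropout. The benefit from interim visits is small and depends on patients actually lacking a week-12 score. The article does not show that the stated test is invalid or that its result would be biased.

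**What to change.** In section 3.3, for the Seattle and quality-of-life scores, replace the before-after comparison with a mixed model for repeated measures on all randomised patients with at least one post-baseline score. Include treatment, visit, treatment-by-visit, baseline score, sex and number of diseased vessels. Take the week-12 treatment difference with its 95% CI as the single test per scale. Treat the TCM syndrome score the same way as a continuous measure, and keep the Table 2 categories under the count-data tests.

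Specify the covariance structure in advance. An unstructured matrix has 5 × 6 / 2 = 15 parameters with 5 visits or 6 × 7 / 2 = 21 with 6, so with 66 patients a fallback should be named. Reconcile the schedules in sections 2.2 and 2.7 first, because they define the visits in the model.

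The cost is a change of wording and one mixed-model procedure per scale in SAS, which the plan already uses. No visits or data are added. The downside is slightly more complex modelling and reporting. The change should be made before unblinding.

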### 3.4. Quality Control

Before the start of the clinical trial, all investigators in the clinical study will participate in Good Clinical Practice (GCP) training, including the GCP regulations and standard operating procedures. All investigators are trained in research protocols and procedures, will read and understand the content of the clinical study protocol, master the principles of GCP, unify the recording methods and judgment standards, and strictly follow the protocol. All participants in the test will have clear responsibilities, act according to the rules, and assume their own responsibilities.

After completing the CRF, it will be submitted to the data statistics center in time for data verification and data locking. Data verification will include manual verification and data verification meetings. The researcher or the personnel designated by the researcher shall correct any inconsistent data found in the verification. Following confirmation that the CRF data are correct at the verification meeting, the main investigator, sponsor, and statistical analyst will sign the relevant documents to lock the test data. The locked data are not allowed to be changed in principle. Data problems discovered after a data lock will be confirmed for revision and documented in accordance with the provisions of the data management plan.

### 3.5. Trial Status

This is an ongoing experiment. By December 2020, the trial had passed the ethical review and clinical study registration, and the project kickoff meeting was successfully held. Subjects are currently being recruited for this study.

## 4. Discussion

PCI can rapidly open severe stenosis and occlusion vessels, and is currently one of the main methods of revascularization [22]. However, according to the data from the British ORBITA study [23], PCI has no significant impact on angina attack and exercise endurance in patients with stable coronary heart disease. Additionally, PCI may lead to myocardial reperfusion injury, local vascular endothelial injury, and in-stent restenosis, all of which may induce the recurrence of cardiovascular events in serious cases [24–26]. Therefore, CR treatment is an urgent need. At present, exercise rehabilitation is widely used in patients with coronary heart disease and other cardiovascular diseases, and has become an important component of the research on CR after PCI [27]. However, patient participation is low, and it is difficult to adhere to it for a long time, which greatly reduces the effectiveness of CR.

The advantages of TCM in CR after PCI have gradually emerged in recent years, and the integration of traditional Chinese and Western medicine has achieved remarkable curative effects [28, 29]. Additionally, for patients who are unsuitable for exercise rehabilitation after PCI, the treatment of integrated Chinese and Western medicine shows great value in improving their prognosis. At present, QSYQ have been incorporated into PCI in TCM diagnosis and treatment of postoperative chest pain expert consensus (2014) and into the expert consensus on Phase 1 CR of integrated traditional Chinese and Western Medicine (2016). In this study, patients with stable angina pectoris caused by Qi deficiency and blood stasis after interventional coronary heart disease (CHD) were selected as the research objects. Using a randomized, double-blind, placebo-controlled method, the peak oxygen consumption was taken as the main efficacy evaluation index to study the effect of Qishen Yiqi dripping pills on exercise endurance and quality of life of patients after PCI.

The main hypotheses of this study are as follows: (1) most patients with CHD after interventional surgery suffer from Qi deficiency and blood stasis, and the long-term application of compound TCM to replenish Qi and activate blood circulation improves exercise endurance, reduces the risk of angina pectoris, reduces the rate of readmission, and improves quality of life; and (2) the effect of integrated traditional Chinese and Western medicine on CR is better than that of traditional exercise rehabilitation. The innovation points are mainly reflected in the following three aspects:A standardized measurement is needed to effectively assess changes in exercise endurance before and after treatment. We chose the rate of change of peak oxygen consumption (PeakVO_2_), the gold standard of exercise endurance, as the main result. Considering the indications and contraindications of cardiopulmonary exercise, patients with stable angina pectoris after coronary heart disease intervention were selected as the research object to avoid the occurrence of cardiovascular events, such as acute myocardial infarction, unstable angina pectoris, and malignant arrhythmias, caused by exercise.This program can give full play to the advantages of syndrome differentiation and treatment, early intervention, and multitarget of TCM and supplement the deficiency of simple rehabilitation methods of Western medicine. After syndrome differentiation, we will include patients with stable angina pectoris of Qi deficiency and blood stasis type. On the basis of conventional Western medicine treatment, QSYQ and placebo will be given orally.The study protocol was designed according to international clinical trial principles. A blank placebo randomized double-blind control was designed to ensure the authenticity and reliability of the research data. To reduce the selection bias caused by the number of enrolled cases, we used stratified randomization. Two stratification factors, “sex” and “number of disaffected vessels,” were set for randomization, with the purpose of reducing type I errors, improving the assurance of small sample trials and ensuring the balance of sample distribution between groups.

## Figures and Tables

**Figure 1 fig1:**
[figure not shown]
Research flowchart.

**Figure 2 fig2:**
[figure not shown]
Research technology roadmap.

**Table 1 tab1:** Diagnostic criteria of Qi deficiency and blood stasis syndrome.

	Signs and symptoms
Symptoms	A: fatigue, shortness of breath, and physical weakness, with aggravation after activity; B: purple and dark lip color
Tongue presentation	The tongue is dark or has ecchymosis and ecchymosis; the sublingual vein is tortuous, dilated, and dark purple
Pulse condition	Weak pulse, astringent pulse
Diagnosis	One of A and one of B; or one of A and one abnormal tongue presentation pulse image for clinical diagnosis reference

**Table 2 tab2:** TCM syndromes observation table.

Definition	Meaning
Clear effect	Clinical symptoms and signs were significantly improved, and the syndrome score was reduced by 70%
Valid	Clinical symptoms and signs were improved, and the syndrome score decreased by 30%
Invalid	Clinical symptoms and signs were not significantly improved, or even aggravated, and the syndrome score was reduced by <30%
Aggravation of symptoms	Clinical symptoms and signs were aggravated, and the syndrome score decreased by < 0

## Data Availability

In order to facilitate follow-up tracing and verify the results of an article, the study data related to the trial will be uploaded and made public at the end of the trial. The data that support the findings of this study are openly available in the “China Clinical Trial Registry” (http://www.chictr.org.cn). The registration number is ChiCTR2000040838 (registration date is December 11, 2020).
